**Adverse event**
Any untoward medical occurrence in a trial participant that does not necessarily have a causal relationship with this treatment (eg, consuming >25 units of alcohol in a 24-h period).
**Adverse reaction**
Any untoward and unintended medical occurrence in a trial participant that is related to the intervention (eg, reaction to a questionnaire).
**Unexpected adverse reaction**
An adverse reaction where the nature and severity of the reaction are inconsistent with the information known about the study.
**Serious adverse event, serious adverse reaction, or unexpected serious adverse reaction**
Any adverse event, adverse reaction, or unexpected adverse medical event reaction that (1) results in death, (2) is life threatening or requires immediate safeguarding, (3) requires hospitalization or prolongs existing hospitalization, or (4) results in persistent or significant disability or incapacity.

### Project Management Group

Project oversight will be provided by a project management group (PMG). The PMG will be chaired by the principal investigator and attended by all coinvestigators. The PMG will meet every quarter and will be responsible for all aspects of project management, including (1) monitoring the delivery of the scientific results needed to progress the study; (2) monitoring the study against the schedule and act if required; (3) monitoring the study against agreed milestones and the identification of risks to achieving milestones as well as solutions for managing risks and issue resolution; (4) providing access to appropriate resources necessary for project progression, including internal and outsourced resources and the management of these resources; and (5) regular review of a blinded report from the study clinician about adverse and serious adverse events (ie, total numbers pooled across arms).

PMG members will be blinded to treatment allocation.

### Executive Steering Committee

An executive steering committee will oversee safety requirements and make recommendations to the PMG. This committee will consist of an independent chair and the study clinician. The committee will receive regular reports from the trial statistician (researcher EC) and the RA on risk and appraise study functions. Concerns and recommendations will be raised with the principal investigator and discussed at PMG meetings.

### Protocol Amendments

Protocol amendments will be discussed and approved by the PMG as well as the PAB and minuted. They will be reported in subsequent closed reports (eg, prepared by the unblinded trial statistician). Any approved amendments will be submitted to the King’s College London ethics committee for approval and published on the Open Science Framework.

### Statistical Analysis

We will describe participant characteristics using appropriate summary statistics (eg, frequency and percentage for categorical items and mean and SD or median and IQR for continuous items).

We will analyze the primary outcome using a linear mixed effect model. The outcome will be the 3 repeated outcome assessments (collected on days 28, 56, and 84). The model will include (1) the baseline measure of the outcome (day 0); (2) a dummy variable indicating treatment allocation (0=control arm and 1=intervention arm); (3) time, measured as weeks since baseline; (4) a treatment × time interaction; and (5) baseline characteristics associated with missingness. The model will additionally include a participant random intercept to account for repeated assessments clustered within individual participants and an unstructured residual covariance matrix. The mixed model will use all available information, retaining participants with at least 1 follow-up assessment, to improve efficiency. Treatment effects (adjusted between-group mean differences in alcohol units) will be estimated from the model for each follow-up separately. Cohen *d* effect sizes at 28, 56, and 84 days will be calculated as the adjusted mean difference divided by the sample SD of the outcome at baseline. The threshold for statistical significance is *P*<.05.

The intention-to-treat analyses will include all participants who complete at least 1 follow-up assessment (day 28, day 56, or day 84).

Analyses will be conducted using Stata (StataCorp LLC) or R statistical software (R Foundation for Statistical Computing).

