**Methods:**

In this 2-arm single-blinded RCT, a smartphone app that includes interactive user-focused features tailored toward the needs of female veterans and designed to enhance participants’ motivations to reduce the amount of alcohol they consume is compared with the UK Chief Medical Officer guidance on alcohol consumption. The trial will be conducted among women who have served at least 1 day of paid service in the UKAF. Recruitment, consent, and data collection will be carried out automatically through the DrinksRation app or the BeAlcoholSmart platform. The primary outcome is change in self-reported weekly alcohol consumption between baseline (day 0) and the 3-month follow-up (day 84) measured using the Timeline Follow Back for alcohol consumption. The secondary outcome is the change in the Alcohol Use Disorders Identification Test score measured at baseline and 3-month follow-up between the control and intervention groups. The process evaluation measures include (1) app use and (2) usability ratings as measured by the mHealth App Usability Questionnaire.

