### Sample Size Calculation

A power calculation was performed based on previously reported data from the DrinksRation RCT [12]. With 148 participants (n=74, 50% per arm), we will have at least 80% power to detect a difference in alcohol consumption of 3 units (approximately 30 g of alcohol/wk) between the intervention and control arms at the 84-day follow-up assessment. This calculation assumes an SD of 5.6 units, an attrition rate of 40% by day 84, a correlation between successive follow-up assessments of 0.7, and an α of 5%.

We have chosen a minimum difference of 3 units based on treatment effects observed in similar studies [26-28] and in reductions observed in the DrinksRation feasibility trial [11] and the confirmatory RCT among help-seeking veterans [12], which found reductions at 28 days of 22 units between the arms. We have chosen a smaller minimum difference of 3 units, recognizing that treatment effects for brief interventions reduce over time and that the target population for this study is not a help-seeking population.

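### Time in weeks with a single treatment × time term most naturally means linear time, which would tie the day-84 primary effect to the earlier visits; the coding should be stated as categorical

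*Protocol article*

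**What the plan says.** The primary time point is day 84: "The primary outcome is change in self-reported weekly alcohol consumption between baseline (day 0) and the 3-month follow-up (day 84" (Abstract, Methods).

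The Statistical Analysis section specifies one linear mixed model for all follow-ups: "The outcome will be the 3 repeated outcome assessments (collected on days 28, 56, and 84". Besides the baseline value and covariates linked to missingness, the fixed effects are "a dummy variable indicating treatment allocation (0=control arm and 1=intervention arm"), then "time, measured as weeks since baseline; (4) a treatment × time interaction". The covariance part is "a participant random intercept to account for repeated assessments clustered within individual participants and an unstructured residual covariance matrix". The output is described as follows: "Treatment effects (adjusted between-group mean differences in alcohol units) will be estimated from the model for each follow-up separately". Cohen d is to be reported at each of the three visits.

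The Sample Size Calculation section explains the 3-unit target at day 84 as a reduced effect, "recognizing that treatment effects for brief interventions reduce over time". It cites a 22-unit difference at 28 days from the earlier trial in help-seeking veterans. It gives no shape for the decline.

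**The concern.** Treatment is expressly called a dummy variable. Time is given a unit and no coding, and the interaction is singular. Anyone programming the model from this list would probably enter weeks as one numeric covariate. The treatment effect is then an intercept plus a slope: two parameters for three visit-specific effects. The day-84 effect becomes a point on a fitted line, so it depends on what happened at days 28 and 56. That sits badly with the promise of separate effects at each follow-up.

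At stake is the confirmatory estimate. If the effect curve bends between week 4 and week 12, the day-84 estimate is biased even with perfect data. The day-28 effect enters with a negative weight, so a larger early benefit lowers the estimated benefit at day 84.

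**Working it through.** **The plan's own figure.** The stated 148 can be reproduced from SD 5.6, a difference of 3, correlation 0.7, two-sided α 5%, 80% power and 40% attrition, if the comparison is of the mean of three follow-ups. The variance factor is (1 + 2 × 0.7)/3 = 0.80, so n = 2 × (1.96 + 0.842)² × 5.6² × 0.80 / 3² ≈ 43.8, that is 44 per arm. Then 44/0.6 gives 74 per arm, 148 in all. This confirms the inputs but says nothing on how time is coded. The powers below are for the day-84 contrast and are not directly comparable with the 80%.

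**Rank of the mean model.** Two arms × three visits make 6 cell means. Intercept, treatment, weeks and treatment × weeks give 4 parameters. Writing e28, e56 and e84 for the benefit at each visit, numeric time forces e28 − 2·e56 + e84 = 0. With visit as a factor there are 6 parameters for 6 cells, and no constraint.

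**Weights at day 84.** Fit a line through weeks 4, 8 and 12 (mean 8, sum of squared deviations 32) and evaluate it at week 12, with complete data and exchangeable correlation. Each weight is 1/3 + (week − 8) × 4/32:
- day 28: 1/3 − 1/2 = −1/6
- day 56: 1/3
- day 84: 1/3 + 1/2 = 5/6

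The bias is therefore −(e28 − 2·e56 + e84)/6.

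**With attrition.** Take 74 per arm, SD 5.6, exchangeable correlation 0.7 and monotone loss of 20/30/40%. Only the final 40% is in the protocol; the path to it is assumed. The weights become −0.185, 0.370 and 0.815. Without baseline adjustment the day-84 standard error is 1.070 (linear) or 1.105 (categorical). With baseline adjustment, assuming baseline correlates 0.7 with each follow-up, it is 0.776 or 0.826. Power is Φ(estimate/SE − 1.96). All effect curves are assumptions.

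| True benefit, days 28/56/84 | Day-84 fit, linear time | Power, linear v categorical, unadjusted | Same, baseline-adjusted |
|---|---|---|---|
| 9/6/3 (straight line) | 3.00 | 80% v 77% | 97% v 95% |
| 6/4/3 | 2.81 | 75% v 77% | 95% v 95% |
| 10/4/3 | 2.07 | 49% v 77% | 75% v 95% |
| 6/6/3 | 3.56 | overstated | overstated |

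The fitted values are for the unadjusted model; adjustment moves them by about 0.02 or less. Example: 10/4/3 gives −0.185 × 10 + 0.370 × 4 + 0.815 × 3 ≈ 2.07, and 2.07/1.070 − 1.96 = −0.02, so power is 49%.

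**Sensitivity to the correlation pattern.** If 0.7 between successive assessments means that correlation decays with distance (AR(1)), the unadjusted 10/4/3 fit is 2.42 and power is 58% against 76%. The bias falls from 0.93 to 0.58 units.

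**The case against.** The strongest reply is that the text never says linear, continuous or slope. With visits only at weeks 4, 8 and 12, weeks since baseline may name the time scale rather than the coding. The unstructured covariance, the per-visit effects and the per-visit Cohen d all fit visit as a factor, and an analysis plan not shown may say so. This stands as a limit on certainty: numeric time is the more natural reading, not a stated fact. It does not remove the need to correct the sentence, because the terms as listed and the output as promised agree only under a coding that the text does not give.

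Three stronger readings are tempting, and the documents do not support them.

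- A reader might infer that a day-84 effect cannot be estimated at all. It can: treatment + 12 × interaction has an estimate, a standard error and a P value. It is constrained, not inestimable.
- A reader might infer from the 22-unit and 3-unit figures that the effect falls fast and then levels off, so that the primary estimate is bound to be too small. The protocol says only that effects shrink. One early value from a help-seeking population shows no curvature, and a straight decline of 22/12.5/3 is fitted at exactly 3. The opposite bend overstates the effect.
- A reader might infer that early visits drive the conclusion. Day 84 still carries 5/6 of the weight with complete data.

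It is also fair to object that the unadjusted powers do not describe the planned model, which adjusts for baseline. Adjustment raises both powers, but for 10/4/3 the gap is still 20 points.

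**Conclusion.** The concern holds in conditional form. As listed, the model most naturally implies linear time. Under that coding the three visit effects are forced onto a line, against the stated intention to estimate each separately, and the day-84 primary estimate can be biased in either direction. In the assumed curves the day-84 fit for a true 3 units ranges from about 2.1 (10/4/3) to 3.6 (6/6/3), and the bias is nil for any straight-line course. The power loss runs from none to 28 points unadjusted, or 20 points baseline-adjusted.

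These sizes rest on the assumed curves, the assumed 20/30/40% dropout path, an exchangeable correlation of 0.7 and, for the adjusted figures, an assumed baseline correlation of 0.7. The exact weights will follow the covariance actually estimated. This should be fixed before the analysis, because it affects the confirmatory estimate and the remedy is cheap. It is not evidence that the trial's result will be wrong.

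**What to change.** State in the Statistical Analysis section, and in any analysis plan, that visit enters as a categorical factor with levels day 28, day 56 and day 84, together with treatment × visit terms. Name the day-84 treatment contrast as the single primary estimate; the day-28 and day-56 contrasts are then secondary.

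The cost is a change of wording and two extra fixed-effect parameters (one for time, one for the interaction). The day-84 standard error grows by about 1% (AR(1), unadjusted), 3% (1.105 v 1.070) or 6% (0.826 v 0.776, baseline-adjusted). If the effect really is linear, that costs 1–3 points of power. No design or data collection change is needed.

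### The primary mixed model is over-parameterised: a participant random intercept cannot be separated from an unstructured residual covariance on three visits, and the protocol does not say which term to drop if fitting fails

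*Protocol article*

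**What the plan says.** The Statistical Analysis section of the protocol article specifies a linear mixed model for weekly units of alcohol: "The outcome will be the 3 repeated outcome assessments (collected on days 28, 56, and 84"). Day 0 is not an outcome row. It enters as a covariate, "the baseline measure of the outcome (day 0"). The fixed part also holds treatment, "time, measured as weeks since baseline", their interaction, and baseline characteristics linked to missingness.

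The covariance part has two components together: "a participant random intercept to account for repeated assessments clustered within individual participants and an unstructured residual covariance matrix". No constraint is placed on the residual matrix, and no alternative structure is given for a fit that fails. On software, the section says: "Analyses will be conducted using Stata (StataCorp LLC) or R statistical software". Treatment effects are read off at each follow-up from the fixed part of the model. The section does not propose to report the variance components.

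**The concern.** An unstructured residual matrix on three visits already describes every variance and covariance that the data can show. A random intercept adds the same constant to all of those elements, so it has nothing left to explain. The likelihood is flat along one direction, and an optimiser has no reason to prefer one split to another.

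This is the primary model of a trial that calls itself confirmatory, and the structure is stated rather than left open. A flat likelihood can stop a routine from converging. The analyst must then drop one of the two terms. The two choices are different models, and the second (random intercept only) forces equal variances and equal correlations on the three visits. Under Randomization and Blinding, the researcher who prepares the statistical reports is unblinded, so the choice is better made in advance.

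**Working it through.** **Inputs.** From Statistical Analysis: three outcome visits, baseline as covariate, time in weeks (4, 8, 12), treatment by time interaction. From Sample Size Calculation: 74 per arm, difference 3 units, SD 5.6, correlation 0.7 between adjacent follow-ups, 40% attrition by day 84, alpha 5%. Assumed here: a two-sided test, linear time, monotone dropout, and the visit SDs in step 5.

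**1. The plan's own figure.** The protocol states: "With 148 participants (n=74, 50% per arm), we will have at least 80% power" "to detect a difference in alcohol consumption of 3 units". The SD of the mean of three follow-ups with common correlation 0.7 is 5.6 × √((1 + 2 × 0.7)/3) = 5.6 × √0.8 = 5.009. Then n per arm = 2 × (1.960 + 0.842)² × 5.009² / 3² = 43.8, so 44. Allowing for attrition, 44/0.6 = 73.3, so 74 per arm and 148 in all. The figure is reproduced and is not in question here.

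**2. Counting parameters.** The marginal covariance is V = τ²J + R, where J is the 3×3 matrix of ones.
- Distinct elements of V: 3 × 4/2 = 6.
- Parameters: 1 (τ²) + 6 (R) = 7.
- The Jacobian of V with respect to the 7 parameters has rank 6. Its null direction is (+1, -1, -1, -1, -1, -1, -1): what is added to τ² can be taken from every element of R.

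**3. The plan's covariance as an example.** Take V = 31.36 × (exchangeable, 0.7). R = V - τ²J has eigenvalues 31.36 × 0.3 = 9.408 (twice) and 31.36 × 2.4 - 3τ² = 75.264 - 3τ². R is therefore a valid covariance matrix for every τ² below 75.264/3 = 25.09. Values of 0, 5, 10 and 20 all return exactly the same V.

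**4. What happens in a fit.** One trial was simulated (n = 148, SD 5.6, correlation 0.7, about 40% monotone dropout).
- With R adjusted to match, the negative REML log-likelihood (constant omitted) was 635.188717 at τ² = 0, 2, 5, 10 and 15.
- Starting values of 1, 5, 10 and 18 ended at τ² = 0.86, 3.28, 5.94 and 13.98. The smallest Hessian eigenvalue was about 2 × 10⁻⁸.
- All four gave a day-84 effect of -4.458 (SE 0.979), equal to five decimals to the unstructured model without the intercept.
- In R (nlme), the model as written returned a fit under two optimisers. The log-likelihood was -930.168, the same as without the intercept, but counted with 12 parameters rather than 11. Fixed effects and SEs agreed to about three decimals.
- The intercept variance differed between optimisers (17.8 and 18.8), and neither fit gave a usable covariance matrix for the variance parameters.
- Stata was not tested.

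**5. Does it matter which term is dropped?** Model-based day-84 SEs were computed with 74 per arm and cumulative loss of about 13%, 27% and 40% at the three visits. The baseline covariate was left out.

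| Assumed true covariance | Unstructured | Random intercept only | Change |
|---|---|---|---|
| SD 5.6, correlation 0.7 throughout | 1.047 | 1.047 | none |
| SD 5.6, 0.7 adjacent, 0.49 for days 28 and 84 | 1.102 | 1.056 | -4% |
| Same decay, SDs 4.6, 5.6, 6.6 | 1.276 | 1.040 | -18% |
| Same decay, SDs 6.6, 5.6, 4.6 | 0.914 | 1.100 | +20% |

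In the third row, the true sampling SE of the random-intercept-only estimate is 1.285, so the reported 1.040 would be anti-conservative. The percentages barely move under other monotone patterns that end at 40%.

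**The case against.** The strongest reply is that only a nuisance split is unidentified. The treatment effect and its SE depend on V, which is identified, and the protocol never undertakes to interpret the intercept variance. This stands, and it sets the limit of the point.

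A reader might infer that the model cannot be fitted or run. The evidence does not support that: one of the two named packages returned a fit with the same treatment effect, and failure in the other is a risk, not something shown. A reader might also infer that time in weeks leaves the unstructured matrix without a visit index. That is wrong: the assessments are fixed at weeks 4, 8 and 12, which is an index. Nor do the documents support any bias in the primary estimate.

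On the unplanned repair, the safeguards deserve mention. Amendments need approval by the project management group, whose members are blinded, and by the patient advisory board. They also go to the ethics committee and are published, and data and code will be shared. Removing the redundant intercept is also the natural repair, and under the exchangeable correlation that reproduces 148 both repairs give the same SE. These arguments lower the stakes. They do not tell the analyst which term to drop, and the sample-size section gives the 0.7 only for adjacent assessments, so exchangeability is not assured.

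A last objection is that covariance detail belongs in a statistical analysis plan. That holds for degrees of freedom and software syntax. It does not cover a structure that the article itself states and that is not identified.

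**Conclusion.** The stated primary model is wrong as written. It has one covariance parameter too many (7 for 6), which makes the variance components and their standard errors meaningless, overstates the parameter count by one in AIC or BIC, and invites convergence failure. That part rests on algebra alone.

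The practical harm is conditional. If the software stops on the flat ridge, the primary result is unaffected. If it fails and only the random intercept is kept, the day-84 SE may be unchanged, about 4% too small, or different by about a fifth in either direction. Those figures rest on an assumed dropout pattern and on assumed correlations and visit SDs, which no one has yet observed in this trial.

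**What to change.** Delete the participant random intercept from the model sentence. Keep the unstructured residual covariance, and state that it is indexed by visit (days 28, 56 and 84) within participant. Name one fallback structure in advance for non-convergence. Since most of the SE error in the check came from unequal variances, a fallback that lets the variance differ by visit, such as heterogeneous Toeplitz, is preferable.

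The cost is a sentence or two. No data collection changes, the sample size stays at 148, and the treatment effect targeted is the same. The degrees-of-freedom method and software commands may be left to the statistical analysis plan.

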### Study Design

#### Overview

This is a 2-arm participant-blinded (single-blinded) confirmatory RCT comparing the DrinksRation smartphone app (intervention arm) with a progressive web application (PWA) presenting NHS-focused drinking advice (named *BeAlcoholSmart*; control arm). The DrinksRation app provides individualized normative advice with features designed to enhance participant motivation, interactive feedback, self-efficacy in modifying their alcohol consumption, and personalized gender-specific messaging. We hypothesize that the intervention arm will be efficacious in reducing alcohol consumption compared with the control arm.

Both the control and intervention arms will be delivered digitally. Participants in the control arm will be given access only to a PWA that comprises a calculator for calculating alcohol units consumed over the previous week, generic public health guidance [20], and weekly reminders to use the calculator (refer to the *Control Arm* subsection for details). Participants in the intervention arm will be given access to the full enhanced DrinksRation app, which includes a range of theoretically driven features and behavioral change messaging (discussed further in the *Intervention Arm* subsection). We have designed this study so that the control arm resembles the intervention arm (eg, an app delivered digitally and usable on a smartphone) but lacks the active ingredients present in the DrinksRation intervention arm (eg, a drinks diary, interactive drinking feedback, and goal setting). This approach was selected to ensure consistency between the arms (both groups receive a digital intervention) and to facilitate participant blinding to treatment assignment.

Participants in both arms will be asked to use the digital interventions for 12 weeks (the intervention period; 84 days). Figure 2 presents the study flow and data collection points.

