#### Control Arm

The control arm will receive access to the BeAlcoholSmart PWA. A PWA is a website that looks and behaves like a smartphone app. The PWA can take advantage of smartphone features such as push notifications and haptics without requiring the participant to download it via an app store. The BeAlcoholSmart PWA will be accessible to participants in the control arm via a unique link. The app will contain a 7-day alcohol unit calculator and generic public health guidance on safe drinking [20]. Participants will also receive reminders via email prompting them to consult the guidance provided as part of the BeAlcoholSmart PWA. Control participants will be invited to complete all questionnaires via Qualtrics (Qualtrics International Inc), with an email reminder being sent when they are due.

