**Inclusion criteria**
Aged ≥18 yearsIdentify as female (self-reported sex)Live in the United KingdomConsume ≥15 UK units (approximately 150 g) of alcohol/wk as measured using Timeline Follow Back for alcohol consumption [24] at baseline (day 0; the choice of a minimum threshold of 15 UK units of alcohol/wk reflects scientific research and UK national guidelines that indicate that regular drinking of >15 units/wk carries increased health risks [25])Are veterans of the United Kingdom Armed Forces (UKAF), defined as per UK definitions as having completed at least 1 day of paid employment in the UKAF (verified by self-report at eligibility screening)Have downloaded the mobile app onto an iOS or Android smartphone

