### Recruitment

Participants will be recruited via an existing research cohort [26] and social media [29] following published recruitment strategies [29,30]. The research cohort will comprise participants from the King’s Centre for Military Health Research health and well-being longitudinal cohort study [26], and participants will be sent an email inviting them to take part. We will also seek to recruit participants via paid promotional advertisements on social media (eg, Twitter, Facebook, and Instagram) with a link enabling potential participants to complete the eligibility and consent survey.

Potential participants who respond to the email invitation or social media advertisements will be sent an email containing an explanation of the study, a link to the participant information sheet, and an invitation to complete the eligibility and consent survey (Multimedia Appendix 2). Eligible participants will then be randomized (refer to the Randomization and Blinding subsection) and sent instructions on accessing the BeAlcoholSmart or DrinksRation app using a unique QR code. Once they have accessed the platform, they can register an account and complete the baseline questionnaire (day 0).

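### The set called intention-to-treat is conditioned on post-randomisation follow-up, and two entry criteria are settled only after allocation, through routes that differ by arm

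*Protocol article*

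**What the plan says.** All references are to the protocol article.

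- **Statistical Analysis.** "The intention-to-treat analyses will include all participants who complete at least 1 follow-up assessment" (day 28, 56 or 84). The mixed model works the same way, "retaining participants with at least 1 follow-up assessment, to improve efficiency". It takes the day 0 value as a covariate and adds baseline characteristics associated with missingness.
- **Ethical Considerations.** All data enter the final analysis, withdrawn participants included, unless a participant asks for deletion.
- **Inclusion criteria (Textbox 2).** One criterion is "Have downloaded the mobile app onto an iOS or Android smartphone". Another is consumption of at least 15 units a week "as measured using Timeline Follow Back for alcohol consumption [24] at baseline (day 0").
- **Recruitment.** After the eligibility and consent survey, "Eligible participants will then be randomized" and sent access instructions. Then: "Once they have accessed the platform, they can register an account and complete the baseline questionnaire (day 0").
- **Study Design, Overview.** "Participants in the control arm will be given access only to a PWA".
- **Control Arm.** The web app runs "without requiring the participant to download it via an app store". Questionnaires go through Qualtrics with an email reminder.
- **Intervention Arm.** All questionnaires are completed in the app, prompted by push notifications.
- **Baseline Measures.** Participants in general are described as having downloaded their respective platforms before the baseline questionnaire.

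**The concern.** An intention-to-treat set is fixed by randomisation. The set defined here is fixed by what participants do afterwards. That matters more than usual in this trial because the behaviour in question is close to the treatment itself. An intervention participant who never installs the app has no described way to give a day 0 or follow-up TLFB. Controls answer through a survey tool reached by email. Two eligibility criteria also fall after allocation, and the article does not say what happens to a randomised person who then fails one of them.

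At stake is the comparability that randomisation provides. If those who drop out of sight differ in drinking from those who stay, and do so differently by arm, the trial could report a contrast among engaged responders as the effect of offering the app.

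**Working it through.** **1. The plan's own figure.** Inputs from Sample Size Calculation: difference 3 units, SD 5.6, correlation 0.7, attrition 40% by day 84, alpha 5% (two-sided assumed), power 80%.

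- Per arm, single measurement: 2 × [5.6 × (1.960 + 0.842) / 3]² = 54.7
- Variance factor for the mean of three follow-ups: (1 + 2 × 0.7) / 3 = 0.80; 54.7 × 0.80 = 43.8, so 44
- Attrition: 44 / (1 − 0.40) = 73.3, so 74 per arm, 148 in total

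The stated 148 reproduces. The point concerns who is analysed, not this number.

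**2. Order of events under Recruitment, against the criteria.**

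| Step | Event | What can be checked |
|---|---|---|
| 1 | Eligibility and consent survey | Age, sex, residence, service, smartphone ownership |
| 2 | Randomisation | – |
| 3 | Access to the allocated platform | App downloaded |
| 4 | Registration and day 0 questionnaire | At least 15 units on the day 0 TLFB |

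The last two criteria come after step 2 in either arm. Read literally, a control never meets the download criterion, because Overview and Control Arm give controls only a web app. Baseline Measures points to a looser meaning that covers both platforms. The timing problem is the same on either reading.

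**3. Who can leave the analysis.** Two conditions apply: a day 0 value (the model covariate) and at least one follow-up.

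- Intervention: both require the app.
- Control: the day 0 questionnaire follows platform access, so controls who never open the web app can also be lost. Later questionnaires are sent through Qualtrics with email reminders. A Table 1 footnote and Outcome Measures describe control data as coming through BeAlcoholSmart, so how far they depend on opening the web app is not settled.

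The routes therefore differ by arm, and loss is possible in both.

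**4. How many.** The 40% is attrition by day 84. Someone seen at day 28 or 56 but not at day 84 stays in the set. If the 40% holds and counts from randomisation, those with no follow-up number at most 0.40 × 148 = 59. The actual share is not given.

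**5. Possible size, under assumptions.** In arm a, let a fraction e be outside the set and drink k units more at day 84 than those retained. The all-randomised mean is the retained mean plus e × k. The shift in the intervention-minus-control difference is then

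−(e_I × k_I − e_C × k_C), where negative favours the app.

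The fractions (averaging the planned 40%) and every k are assumed:

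| e_I | e_C | k_I | k_C | Shift (units) |
|---|---|---|---|---|
| 0.4 | 0.4 | equal | equal | 0 |
| 0.5 | 0.3 | 3 / 5.6 / 10 | same | −0.6 / −1.1 / −2.0 |
| 0.3 | 0.5 | 3 / 5.6 / 10 | same | +0.6 / +1.1 / +2.0 |
| 0.4 | 0.4 | 3 / 5.6 / 7.5 | 0 | −1.2 / −2.2 / −3.0 |
| 0.4 | 0.4 | 0 | 3 / 5.6 / 7.5 | +1.2 / +2.2 / +3.0 |

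These are raw shifts; covariate adjustment would remove whatever part the covariates explain.

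**6. Does baseline adjustment remove it?** Not necessarily. A simulation used no true effect, 74 per arm, 60% retained in each arm, and one follow-up correlated 0.7 with baseline. Retention depended on unmeasured motivation in the intervention arm only (residual correlation of motivation with drinking −0.5). The baseline-adjusted estimate averaged −0.9 units, with about 19% rejection at a nominal 5%. That scenario was built to favour the app; selection in the control arm instead would reverse the sign.

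**The case against.** Participants with no follow-up add no outcome information to a likelihood-based mixed model. If data are missing at random given baseline drinking and the planned predictors of missingness, leaving them out does not by itself bias the estimate. This stands, and it is why the consequence is conditional. It does not rescue the label, and app uptake is not a baseline covariate.

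The eligibility survey (Multimedia Appendix 2, not shown) may already screen drinking, and an unseen analysis plan may hold sensitivity analyses. Their absence from the article is no finding. The article nonetheless ties the 15-unit criterion to the day 0 TLFB and places day 0 after platform access.

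A reader might go further and infer three things that the document does not support:

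- **That only intervention participants can be excluded.** Baseline Measures leaves the meaning of download open, and controls without a day 0 value also leave the model.
- **That the bias favours the app.** The Discussion expects possible disengagement in the control arm because its service is static, while intervention participants get push prompts every few hours on questionnaire days. If the less motivated controls leave more often, the bias could run against the app.
- **That 40% of participants are excluded**, so that a 3-unit effect in responders becomes 0.6 × 3 = 1.8 units overall. The 40% refers to day 84, and zero effect in everyone lost is an assumption.

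**Conclusion.** The point holds on the text in three respects. The set called intention-to-treat is a modified, available-case set, at odds with Ethical Considerations. Two inclusion criteria are settled after allocation. Entry to the analysis runs through platform uptake by different routes in the two arms. None of this depends on arithmetic.

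The effect on the estimate is a possibility and is not shown to occur. It requires missingness that is not at random given the model covariates and that differs by arm. Under the assumed inputs the shift ranges from zero to 3.0 units in either direction, against a target of 3. With equal exclusion and equal differences it is zero. The document fixes neither sign nor size, so no corrected treatment effect should be quoted.

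**What to change.** 1. Delete the download criterion, since smartphone ownership already covers access, or reconcile it with Overview, Control Arm, Recruitment and Baseline Measures.
2. Complete the baseline TLFB and the 15-unit check in the online eligibility survey, before randomisation.
3. Define the intention-to-treat set as all randomised participants, as allocated, whether or not they install or respond, apart from data deleted on request. Align Statistical Analysis and Ethical Considerations with this.
4. Rename the set with at least one follow-up modified intention-to-treat.
5. Offer intervention participants who do not install the app the existing Qualtrics questionnaires.
6. Add one sensitivity analysis of all randomised participants that allows departures from missing at random to vary by arm, for example delta-adjusted multiple imputation.

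Steps 2 and 5 are needed for the rest to work. Moving baseline into the outcome vector (a constrained longitudinal model) would not help alone, because on the present sequence non-installers have no day 0 TLFB.

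The cost is a longer eligibility survey, one extra questionnaire route on a tool already in use, slightly more analysis work, and possibly a smaller or less precise estimate.
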